### Return-On-Investment (ROI) Analyses

We will conduct a budget impact analysis to inform the sustainability of each EBP. Following the VHA recommendation to evaluate cost of projects [70], we will identify the relevant costs associated with implementation of the EBP, the EBP itself, and the consequences of the EBP (e.g., healthcare utilization). Using a micro-costing approach [71], we will collect costs for EBQI-IC and EBQI-LC sites, measuring: 1) implementation costs as one-time costs to develop the intervention; and 2) intervention and downstream costs as costs that would be incurred by facilities adopting the EBPs (e.g., site participants; RIVET implementation team members’ time spent in training, meetings and preparing for meetings; staff time performing the intervention). To capture RIVET implementation team staff time spent in various implementation activities, data will be collected through the implementation facilitation log, administrative documents, and weekly time surveys. For both EBPs, clinical staff will document the estimated time spent to complete EBP through an EHR template. Finally, we will identify the costs of healthcare utilization which may be impacted by the implementation of these EBPs from the VA administrative data, such as change in outpatient utilization (e.g., primary care, social work, mental health, pharmacy) and inpatient utilization. This will be done by estimating the excess cost for patients exposed to the EBP compared to a control group of unexposed patients using multivariable regression models to control for measured confounders. We will use generalized linear models for continuous data and two-part models for semi-continuous data with distributional families chosen to best fit the data. If preliminary data reveals that medication adherence changed with MAA implementation, we will also include changes in pharmacy costs.

We will measure whether EBPs were maintained during each sites’ sustainment period (time period following the 18-month active implementation period), how EBPs spread within the original sites and to new sites, and what factors are associated with maintenance and spread. We will also assess adaptations made to the EBPs in response to changing VHA context.

For sustainment and spread, we will continue to assess receipt of each EBP among top 10% CAN score patients (Reach) longitudinally during the sustainment period by measuring 6 and 12 months after the active implementation phase. We will incorporate Adoption measures to assess spread within the implementation site and in new sites by measuring how many additional staff were trained on each EBP, proportion of staff trained on each EBP, and which types of healthcare staff delivered each EBP (representativeness). We will compare EBQI-IC and EBQI-LC sites to determine which implementation strategy is most effective for sustaining the EBPs. Using the matrix analysis approach described above, we will analyze qualitative interview data to explore the role of contextual factors on sustainment, and the “fit” between context, intervention, and implementation strategy on sustainability.

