#### EBP Medication Adherence Assessment (MAA)

High-risk Veterans often experience complicated medication regimens, potential side effects, and other known barriers to medication adherence [46]. Medication nonadherence represents a common problem among multimorbid patients [47], and is one of the largest contributors to preventable emergency department visits and hospitalizations among high-risk Veterans. Many approaches to improving medication adherence are limited by a focus on particular diseases rather than the entire medication regimen and by a focus on the healthcare providers’ point of view, rather than on patients’ goals and agency around medication taking [48].

A standardized Medication Adherence Assessment (MAA) guides primary care teams to assess for barriers and challenges to medication adherence through open-ended questions and enables primary care teams to understand high-risk patients’ goals and preferences and better impact medication-taking behaviors across the patients’ medication conditions [12, 13]. The MAA prompts the clinician to employ specific strategies around adherence and potentially use motivational interviewing or health coaching if the patient is ambivalent about taking a medication. Health coaching has emerged as an effective, patient-centered, collaborative approach to understand patient goals and preferences and enhance patients’ adherence to modifiable health behaviors [49]. Health coaching is a type of cognitive-based behavior change technique that employs motivational interviewing and goal-setting to guide the patient to change health behaviors, such as diet, exercise, and medication adherence [49]. Meta-analyses have shown that cognitive-based behavior change techniques (e.g., health coaching) to improve medication management are associated with an effect size of 0.34 (95% CI 0.23–0.46) on improved medication adherence [50]. 

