#### EHR Administrative data

VHA CDW contains data on patient characteristics, outpatient encounters, provider types for each encounter, acute and inpatient care utilization, medication fill history, and Healthcare Effectiveness Data and Information Set (HEDIS) quality metric status. Health factor administrative data is generated by templates constructed for each EBP within the EHR. Managerial Cost Accounting (MCA) data will be utilized for the cost analyses.

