#### Reach

Reach is defined in this study as the proportion of high-risk patients on each study team’s panel that received one of the EBPs during the 18-month implementation period. See Table 2 for details on included reach measures. We define “high-risk patients” using a VHA-specific risk score called the Care Assessment Need score, previously developed and validated by VA through machine-learning to predict a patient’s risk for a VHA hospitalization or mortality [54]. We define ‘receipt’ as having the EBP assessment at least partially documented in the electronic health record (EHR). We will also examine the patient characteristics (sociodemographic, Elixhauser comorbidity score [66]) of eligible patients who did vs. did not receive the EBP.

**Table 2 Tab2:** Reach and effectiveness outcomes metrics

	**Reach** **(Primary Outcome)**	**Proximal Care Process Impacts**	**Patient and Provider Impacts**	**Clinical Quality and Outcomes**
EBP 1 CACP	Proportion of site-assigned patients in the top 10% of CAN-hospitalization scores that receive the EBP	• Number and type of referrals generated • Referrals completed by patient • Number of primary care social worker, pharmacist, nurse, integrated MH encounters	• Comprehensiveness of Care (Patient Survey^a^/SHEP) • Self-Management Support (Patient Survey^a^/SHEP) • Primary Care provider experience and perceived support for high-risk patient care (Clinician Survey)	• VHA ACS-related and total acute hospitalizations • VHA ACS-related and total emergency department visits
EBP 2 MAA		• Number and type of referrals or actions documented receiving the EBP • Number of primary care pharmacist, social worker, nurse, integrated MH encounters	• Providers Discuss Medication Decisions/Medication Comprehensiveness (Patient Survey^a^/SHEP) • Self-Management Support (Patient Survey^a^/SHEP)	• Medication adherence (Patient Survey^a^) • Adherence for DM, HTN, HL, MH medications (VHA Pharmacy Data) • HEDIS measures for DM, HTN, HL management

*ACS* Ambulatory care-sensitive, *EBP* Evidence-based practice, *CACP* Comprehensive Assessment and Care Planning, *CAN* Care Assessment Need, *DM* diabetes mellitus, *HTN* hypertension, *HEDIS* Healthcare Effectiveness Data and Information Set, *HL* hyperlipidemia, *MAA* Medication Adherence Assessment, *MH* Mental Health, *PDC* proportion of days covered, *SHEP* Survey of Healthcare Experiences of Patients

^a^Refers to patient survey referenced in the Methods

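### The change in drug costs enters the MAA budget impact only if unspecified preliminary data show that adherence changed, so a real cost change can be counted as zero

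*Protocol article*

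**What the plan says.** All of the cost plan is in the protocol article, Return-On-Investment (ROI) Analyses.

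- Purpose: "We will conduct a budget impact analysis to inform the sustainability of each EBP".
- Scope: implementation, the EBP itself, and "the consequences of the EBP (e.g., healthcare utilization").
- Utilization costs, with no condition attached: "such as change in outpatient utilization (e.g., primary care, social work, mental health, pharmacy) and inpatient utilization".
- Estimator: "estimating the excess cost for patients exposed to the EBP compared to a control group of unexposed patients", by adjusted regression.
- The conditional item: "If preliminary data reveals that medication adherence changed with MAA implementation, we will also include changes in pharmacy costs".

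The article does not say which data are preliminary, which adherence measure is meant, or what size or direction of difference counts as a change.

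Table 2 (under Reach) gives MAA two adherence outcomes: a patient-survey measure and "Adherence for DM, HTN, HL, MH medications (VHA Pharmacy Data"). Under EHR Administrative data, the warehouse already holds "medication fill history, and Healthcare Effectiveness Data and Information Set (HEDIS) quality metric status", and managerial cost accounting data are the stated source for the cost analyses.

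**The concern.** The budget impact is meant to tell facilities what sustaining each EBP will cost. Drug use is the consequence that MAA targets most directly, yet it is the one cost that the section makes depend on a result. Three problems follow.

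- If the preliminary data do not show an adherence change, the drug-cost change is left out. It then counts as exactly zero with no interval, although absence of a detected change is not evidence of no change.
- The trigger may miss what drives the cost. The MAA section describes complicated regimens ("High-risk Veterans often experience complicated medication regimens, potential side effects, and other known barriers to medication adherence") and an assessment that works across a patient's conditions. The pharmacy-data adherence outcome covers only four drug groups, so drug cost can move outside them without that outcome moving.
- When the cost does pass the trigger, it has been selected on a related result and may be exaggerated, depending on how closely the cost and adherence estimates move together.

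At stake is a total-cost figure for MAA that depends on how an early look falls out.

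**Working it through.** **Reading the section against itself.** The scope covers the consequences of the EBP, and utilization is costed with pharmacy named unconditionally. A later sentence then adds changes in pharmacy costs, conditionally and with the word *also*. The reading that makes both true is that pharmacy service use is always costed and drug cost is the conditional extra. The article does not say this. Fill history and cost accounting data are planned sources either way, so the condition is not forced by a lack of data.

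**The two contrasts.** Under Outcomes and data analyses, effectiveness outcomes such as adherence are modelled by the site's strategy assignment. Costs compare patients exposed and unexposed to the EBP. If the trigger uses the first contrast, a null result there can coexist with a drug-cost change among exposed patients.

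**Illustrative size.** The plan has no figure to reproduce: it states no alpha, power, effect size or cost for this point. Assumptions:

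- *changed* means |Z| > 1.96 for the adherence estimate, Z ~ N(m, 1);
- m = 1.96 + z(power), giving m = 1.118, 1.960 and 2.802 for power of 20%, 50% and 80%;
- the cost estimate has signal-to-noise s = m and correlation ρ with the adherence estimate.

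Formulas:

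- P(included) = 1 − Φ(1.96 − m) + Φ(−1.96 − m)
- E = mean of Z − m given inclusion = [φ(1.96 − m) − φ(−1.96 − m)] / P(included)
- mean of the included cost ÷ truth = 1 + ρE/s
- mean of the counted cost ÷ truth, with omission counted as zero = P(included) × (1 + ρE/s)

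Example at 20% power, ρ = 0.8: P = 0.201, E = 1.375, ratio = 1 + 0.8 × 1.375/1.118 = 1.98, counted on average = 0.201 × 1.98 = 0.40.

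| Power for adherence | Omitted | Ratio if included, ρ = 0 | ρ = 0.5 | ρ = 0.8 | Average counted ÷ truth (ρ = 0 to 0.8) |
|---|---|---|---|---|---|
| 20% | 80% | 1.00 | 1.61 | 1.98 | 0.20 to 0.40 |
| 50% | 50% | 1.00 | 1.20 | 1.33 | 0.50 to 0.66 |
| 80% | 20% | 1.00 | 1.06 | 1.10 | 0.80 to 0.88 |

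If adherence truly does not change, the term is still included 5% of the time. A drug-cost change arising without any adherence change would then be omitted 1 − 0.05 = 95% of the time.

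If the cost estimate is noisier than the adherence estimate (s below m), the excess over 1.00 grows in proportion to m/s. The omission column does not change.

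With unconditional inclusion, P(included) = 1 and the selection ratio is 1.00 in every row.

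**The case against.** The strongest reply is that this is one line in a supporting economic analysis, that the section already costs pharmacy without condition, and that a condensed article may leave the definitions of *preliminary* and *changed* to a fuller plan. The first two parts stand and limit the point. The third does not dispose of it: defining the terms would still leave a rule that drops a cost according to an observed outcome.

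Several stronger readings are tempting but not supported.

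- *All pharmacy costs are conditional.* The unconditional mention under outpatient utilization contradicts this. Only the change in drug cost appears to be affected.
- *An included cost is necessarily overstated.* Inflation needs a positive correlation between the cost and adherence estimates. That is plausible if both come from the same fill records, but the planned contrasts differ, and at zero correlation there is none. Assuming that cost moves in strict proportion to adherence gives the extreme case only.
- *An interim analysis drives the switch.* The article speaks of preliminary data and describes no interim analysis.
- *The rule flatters MAA.* The condition is a change in either direction. Omitting a saving would make MAA look worse.
- *CACP's pharmacist encounters go uncosted.* They fall under outpatient utilization, which is costed for both EBPs. Only CACP drug cost is outside, and the article assigns adherence outcomes to MAA alone. It also plans no direct comparison of the two EBPs' budgets.

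**Conclusion.** The point holds in a limited form. As written, the rule makes MAA's drug-cost change disappear whenever unspecified preliminary data fail to show an adherence change, which does not fit the section's aim of counting the EBP's consequences. The omission follows from the text. Its frequency (about 80%, 50% and 20%) rests on the assumed 0.05 trigger and power levels, and the inflation range (none, up to about 2.0, 1.3 and 1.1 times) also on the assumed correlation and equal signal-to-noise. For a true change, the counted cost is pulled toward zero on average in every case tabulated. Its direction and monetary size cannot be known from the article. The change is worth making because the result informs sustainment decisions. The primary outcome is unaffected.

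**What to change.** Replace the conditional sentence with one to this effect: *The change in outpatient drug costs will be estimated from fill and cost data for all outpatient medications and included in the budget impact with its uncertainty, whatever the adherence result.* Apply it at least to MAA, and preferably to both EBPs from the same administrative data.

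Report totals with and without drug costs. State what pharmacy covers under outpatient utilization (service use, dispensing, drug cost) so that nothing is counted twice.

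The cost is small: one or two sentences and one more category from sources already planned. The downside is that drug cost is variable, so the interval for total cost may be somewhat wider.

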## Discussion

The RIVET project aims to implement two evidence-based assessments to improve the management of the high-risk patient population within VHA primary care using two EBQI strategies. This work will add to a much needed body of literature evaluating the effectiveness of different approaches to EBQI to implement EBPs within primary care [1]. It is the first study to compare the effectiveness of EBQI conducted with individual sites (EBQI-IC) vs conducted with groups of sites as a learning collaborative (EBQI-LC) and to compare which implementation strategy is most effective under various contexts accounting for unique barriers, facilitators, and adaptations. Additionally, RIVET will provide evidence on which of the two strategies is the most cost-efficient strategy. Comparing EBQI-LC and EBQI-IC will allow our VHA primary care leaders to tailor the implementation strategy to the primary care context in preparation for widespread implementation. While our project focuses on EBPs for high-risk patients, we anticipate that this comparison of EBQI strategies can inform those implementing EBPs with other primary care patient populations.

The EBPs aim to systematically identify modifiable risk factors within primary care for patients with complex needs—enabling primary care to provide comprehensive and holistic care. Furthermore, by selecting the most effective, less burdensome, and less costly implementation strategy ensures greater buy-in from clinical leadership interested in offering advanced primary care and frontline staff who are often overwhelmed with clinical demands and chronic staffing shortages.

We anticipate several potential challenges to optimal implementation. The major challenge for the RIVET project is that, as with any project embedded in pragmatic healthcare system operations, it is vulnerable to national and local VHA contextual factors. Specifically, success of the project can be compromised by VHA staffing changes within the sites and study teams. In addition, since primary care teams are tasked with a wide variety of care, new health system initiatives and external circumstances (e.g., pandemic-induced changes in care delivery) can unexpectedly compete with high-risk patient care priorities. In addition, the active implementation period requires 18-month engagement from clinical champions to learn EBQI practices and to properly use the EBP in their routine care of high-risk patients. Finally, RIVET EBQI IC and LC sessions will be held virtually. Although most provider training has moved to virtual modalities post-Covid, the best methods to keep staff engaged may vary over time and setting. The RIVET project will not only implement EBP tools that will help better manage high-risk Veterans at 16 VA sites but will provide the tools and evidence on the best implementation strategies for primary care staff at VHA working to improve high-risk patient care and primary care delivery.

## Data Availability

Data sharing is not applicable to this article as no datasets were generated or analyzed during the current study.

## Abbreviations

ACS: Ambulatory care-sensitive
CACP: Comprehensive Assessment and Care Planning
CAHPS: Consumer Assessment of Healthcare Providers and Systems
CAN: Care Assessment Need
CFIR: Consolidated Framework for Implementation Research
CGA: Comprehensive Geriatric Assessment
CPC +: Comprehensive Primary Care Plus
CDW: Central Data Warehouse
EBP: Evidence-based practice
EBQI: Evidence-Based Quality Improvement
ED: Emergency department
EHR: Electronic health record
HEDIS: Healthcare Effectiveness Data and Information Set
IC: Individual coaching
LC: Learning collaborative
MAA: Medication Adherence Assessment
MCA: Managerial Cost Accounting
OPC: Office of Primary Care
PACT: Patient-Aligned Care Team
PCMH: Patient-Centered Medical Home
PCP: Primary care provider
PRAPARE: Protocol for Responding to and Assessing Patients’ Assets, Risks, and Experiences
PRISM: Practical, Robust Implementation and Sustainability Model
QUERI: Quality Enhancement Research Initiative
RCT: Randomized control trial
RE-AIM: Reach, Effectiveness, Adoption, Implementation, and Maintenance
RIVET: High-RIsk VETerans
ROI: Return-On-Investment
SHEP: Survey of Healthcare Experiences of Patients
VHA: Veterans’ Health Administration
